### **6.7 Photographs of Rash or Injection Site Reactions**

If a subject develops a rash or injection site reaction, photographs may be taken by the investigators. These photographs will not include the subject's face or any identifying scars, marks, or tattoos.

### **6.8 Contraindications to Vaccination**

The following criteria should be checked prior to each immunization and are contraindications to further immunization. The subject will be encouraged to remain in the safety evaluation for doses already received.

- Hypersensitivity reaction following administration of the study vaccine.
- Positive urine or serum  $\beta$ -hCG test.
- Urine dipstick more than trace positive for blood or protein, confirmed by urinalysis. Should a female subject's urine dipstick show more than trace blood, she will not be excluded from vaccination if she is currently menstruating.

## 6.9 Indications for Deferral of Vaccination

If any one of the following AEs occurs at the time of the scheduled vaccination, the subject may be either vaccinated at a later date within the allowable time interval specified in the protocol or withdrawn at the discretion of the Investigator:

- Oral temperature  $>37.5^{\circ}\text{C}$  at the time of vaccination will warrant deferral of immunization until fever resolves (within protocol-defined vaccination window).
- Any other condition that in the opinion of the Investigator poses a threat to the individual if immunized or that may complicate interpretation of the safety of vaccine following immunization.

Such individual(s) will be followed in the clinic until the symptoms resolve or the window for immunization expires. No further vaccination will be performed if the subject does not recover (oral temperature  $\leq 37.5^{\circ}\text{C}$  and/or lack of symptoms) within the vaccination window. The subject will be monitored for safety and immunogenicity for 12 months after their last vaccination. If the subject does not receive the second or third vaccination, some scheduled safety blood draws may not be performed at the discretion of the PI. Blood draws scheduled to measure immune response will be obtained if possible. If the subject meets any of the above criteria for deferral on the day of first immunization, the Investigator may elect to exclude the subject from further participation in the study. Eligible alternate subjects will be vaccinated instead.

## 6.10 Subject Withdrawal Criteria

A subject will not be considered to have completed the trial if any of the following reasons apply:

1. *Research terminated by Sponsor or Investigator* – applies to the situation where the entire study is terminated by the Sponsor or Investigator, or other regulatory authority for any reason.
2. *Withdrawal of consent* – applies to a subject who withdraws consent to participate in the study for any reason.
3. *Noncompliant with protocol* – applies to a subject who does not comply with protocol-specific visits or evaluations, on a consistent basis, such that adequate follow-up is not possible and the subject's safety would be compromised by continuing in the trial. This also applies to a subject who is lost to follow-up and is not reachable by telephone or

other means of communication; and is not able to be located.

4. *Developed an AE* - applies to a subject who is withdrawn from study due to an AE, serious or otherwise. Any grade 3 or greater AE that is assessed as possibly, probably, or definitely related to vaccination (other than local reactions lasting <72 hours, or systemic reactions lasting <24 hours) will result in withdrawal of the subject from further vaccinations. Subjects may also be withdrawn for any AE that would cause continued participation in the study to not be in the best interest of the subject, as per the investigator's judgment. Any subject who is withdrawn from the study because of an AE related to study agent will be followed for safety until at least resolution of that AE and will be encouraged to remain in the safety evaluation for the duration of the study.
5. *Other* – is used when previous categories do not apply and a written explanation is required.

If a subject withdraws or is withdrawn prior to completion of the study, the reason for this decision will be recorded in the source documents and CRIMSON Data System. Any subject who has received at least 1 dose of vaccine will be encouraged to remain in the safety evaluation for the duration of the study. The subject's data will be included in the safety and immunogenicity analysis. If a subject fails to complete all planned vaccinations because of an AE or serious adverse event (SAE), the subject will be followed until resolution or stabilization of the event. If a subject withdraws, the investigator will make a reasonable effort to determine the reason.

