### **6.11 Replacement of Subjects**

Subjects who have received at least 1 vaccination and who withdraw or are terminated from the study prior to completion will not be replaced.

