### **Serious Adverse Events**

A Serious Adverse Event (SAE) is defined as an AE that results in any of the following outcomes:

- death
- life threatening (i.e., an immediate threat to life)
- inpatient hospitalization or prolongation of an existing hospitalization
- a persistent or significant incapacity or substantial disruption of the ability to conduct normal life functions
- congenital anomaly/birth defect
- other medically important event\*

\* Medical and scientific judgment will be exercised in deciding whether expedited reporting is appropriate in other situations, such as important medical events that may not be immediately life threatening or result in death or result in hospitalization but may jeopardize the patient or may require intervention to prevent one of the other outcomes listed above. These will also usually be considered serious.

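### Section 6.10 item 4 exempts short related reactions from mandatory withdrawal with no grade ceiling, leaving re-dosing after a short, non-serious Grade 4 reaction to investigator discretion

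*Protocol*

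**What the plan says.** Section 6.10 item 4 sets the individual stopping rule. A related adverse event (possibly, probably or definitely) of Grade 3 or greater ends vaccination for that subject, with one carve-out: "other than local reactions lasting <72 hours, or systemic reactions lasting <24 hours) will result in withdrawal of the subject from further vaccinations". For whatever the carve-out releases, the same item leaves a discretionary clause: "Subjects may also be withdrawn for any AE that would cause continued participation in the study to not be in the best interest". That decision is left to the investigator.

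Two other sections bear on the next dose:

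- Section 6.8 lists three contraindications. The only one that concerns a reaction to the vaccine is "Hypersensitivity reaction following administration of the study vaccine". The others are a positive pregnancy test and an abnormal urine dipstick.
- Section 6.9 allows deferral or withdrawal for events present when a dose is due, including "Any other condition that in the opinion of the Investigator poses a threat to the individual if immunized".

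Section 9.5 adds six study-level halting rules, and Appendix C defines the grades. On the consequences of withdrawal, Section 6.10 says "The subject's data will be included in the safety and immunogenicity analysis", and Section 6.11 says that vaccinated subjects who leave "will not be replaced".

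**The concern.** The rule is mandatory from Grade 3 upward, yet its exception takes no account of grade. Read literally, a related Grade 3 systemic reaction of 24 hours compels withdrawal, while a related Grade 4 systemic reaction of 23 hours does not. Appendix C heads its Grade 4 column as potentially life threatening.

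This conjugate is being given to humans for the first time (Section 1.3). What is at stake is whether a subject who has just had the worse grade of reaction is kept from the next dose by a written rule or only by individual judgement.

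**Working it through.** The protocol states no figure on this point, so the check applies the rules as written.

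**Step 1: item 4 as a rule.** Withdrawal is mandatory if grade ≥ 3 AND related AND NOT [(local AND duration < 72 h) OR (systemic AND duration < 24 h)]. For a related reaction on either side of each limit:

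| Grade | Local 71 h | Local 72 h | Systemic 23 h | Systemic 24 h |
|---|---|---|---|---|
| 2 | no | no | no | no |
| 3 | no | yes | no | yes |
| 4 | no | yes | no | yes |

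The Grade 3 and Grade 4 rows are identical, so the exemption has no grade ceiling.

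**Step 2: does another fixed rule catch the exempted Grade 4 cells?** Take one subject with a short, related Grade 4 reaction.

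- 6.8 applies only if it was hypersensitivity.
- 6.9 is discretionary and addresses conditions present when a dose is due. A reaction that cleared within 24 or 72 hours will normally be over by the next dose, planned about two months later (Day 0 to Day 56, Day 56 to Day 120).
- 9.5 rule 1 needs a related serious adverse event.
- 9.5 rule 2 needs hypersensitivity.
- 9.5 rule 3 needs one severe clinical illness without an unrelated diagnosis to account for it. It is not tied to a grade.
- 9.5 rule 4 needs two subjects in a dose cohort and, for systemic events, names Grade 3.
- 9.5 rule 5 is erythema nodosum.
- 9.5 rule 6 needs two subjects and covers only induration and abscess.

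If the event is not hypersensitivity, not judged serious and not judged a severe illness, nothing mandatory remains.

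**Step 3: which events are left?** Section 9.1 makes an event serious if, among other criteria, it is an immediate threat to life or involves "inpatient hospitalization or prolongation of an existing hospitalization". Against that, Appendix C grades as follows:

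- Fever above 40 °C is Grade 4 on the reading alone.
- Headache, malaise, myalgia and arthralgia are Grade 4 on an emergency-room visit, admitted or not. Injection-site pain is the same.
- Nausea needs a visit or admission for hypotensive shock, and urticaria would probably be barred under 6.8, so neither is counted.
- Grade 4 erythema, swelling and induration mean necrosis (or, for erythema, exfoliative dermatitis), which is unlikely to clear within 72 hours.
- Events not listed in Appendix C, such as pruritus, are Grade 4 under 9.3.2 only when life-threatening, and so would be serious.

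That leaves 5 of the 7 solicited systemic events in Table 3 and 1 of the 5 solicited local reactions (pain) that can reach Grade 4 without admission. These are counts of symptoms, not frequencies.

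**The case against.** The strongest reply is that the remaining gap is thin. Section 9.1 counts as serious an event that "may jeopardize the patient or may require intervention to prevent one of the other outcomes listed above", and adds that such events will usually be treated that way. A related Grade 4 reaction judged serious triggers halting rule 1 in one subject and stops all dosing until the safety committee and sponsor have reviewed it. Rule 3 also needs only one subject, and a reaction attributed to the vaccine is hard to explain by an unrelated diagnosis. Several of the Grade 4 examples measure care-seeking rather than severity: a same-day emergency visit for a possibly related headache is a fair matter for judgement. Vaccination criteria are also reviewed before each repeat dose.

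Most of this stands, and it is why the point is minor. It does not close the gap. Both routes still depend on judgement, neither is linked to Grade 4, and fever above 40 °C is graded on the reading alone.

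Timing also limits the benefit. Accrual was planned for about September 2011, which puts Day 300 around mid-2012, while this text is Version 6.0 of January 2013. Section 3.1 already cites preliminary results over the first three doses. Actual dosing dates are not given, so a change now might protect few doses or none. The number of planned repeat doses is therefore no measure of the problem.

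A reader might infer that every related serious reaction should permanently bar the subject, because a short one does not compel withdrawal once a halt is lifted. The document does not support going that far: rule 1 already puts those events before the committee and the sponsor, and nothing shows that review to be inadequate.

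**Conclusion.** The point holds in a narrow form. As written, item 4 lets a short, related Grade 4 reaction escape a mandatory rule that a slightly longer Grade 3 reaction does not. For a single such reaction that is neither hypersensitivity nor judged serious or a severe clinical illness, only investigator discretion governs the next dose.

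This rests on reading the exemption literally. The authors may have had only Grade 3 in mind, but the text does not say so. It also rests on Grade 4 in Appendix C not being automatically serious under 9.1.

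It would be wrong to infer that the protocol allows re-dosing after Grade 4 reactions in general. Those that are serious or severe illnesses halt the study for review, hypersensitivity is barred by 6.8, and those past the time limits already end vaccination. Nor can a frequency be attached: the document gives no rate for such reactions and none is assumed here. An investigator could withdraw the subject in any case. This is a cheap improvement of minor priority.

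**What to change.** In 6.10 item 4, insert the words Grade 3 before each of the two exempted categories, local and systemic, leaving the 72-hour and 24-hour limits as they are. In 6.8, add one bullet to the list checked before each dose: *Any related Grade 4 reaction to a prior dose of the study vaccine*. Short Grade 3 reactions keep their present tolerance, and serious reactions below Grade 4 stay with the existing halting review. If no doses remain under this version, carry the corrected wording into the Phase 1b study foreseen in Section 1.4.

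The cost is one clause and one bullet in an amendment, plus at most a very few subjects losing later doses. Their data stay in the analyses but they are not replaced. One such withdrawal after dose 1 would leave 5 − 1 = 4 of 5 subjects in Group 1a or 1b, or 20 − 1 = 19 of 20 in Group 2, with a true post-dose-2 antibody value for the dose comparison in Section 11.3. In a group of five that is a loss of 1/5 = 20%, which is the main argument for keeping the change to Grade 4.

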### **6.11 Replacement of Subjects**

Subjects who have received at least 1 vaccination and who withdraw or are terminated from the study prior to completion will not be replaced.

### **6.12 Treatments that Could Potentially Interfere with Vaccine-induced Immunity**

Treatment with any of the following medications during the study may exclude a subject from receiving further doses of the study vaccine. However, the subject will be encouraged to remain in the study for the duration of the study for safety evaluations.

- Licensed vaccine in the 2-week period (4 weeks for live vaccines) prior to and following each vaccination
- Receipt of immunoglobulins and/or any blood products up to 6 months prior to the first vaccination through 30 days after administration of the last dose of vaccine
- Chronic oral or intravenous administration ( $\geq 14$  days) of immunosuppressive doses of steroids, i.e., prednisone >10 mg per day, immunosuppressants or other immune-modifying drugs from each day of vaccination to 2 weeks following each vaccination
- Any investigational drug or investigational vaccine other than the study vaccine during the study period

- Required surgical removal of the spleen or the development of a hematologic or other disease that would interfere with normal immunity.

### **6.13 Clinical Laboratory Testing**

Using standard techniques, the clinical laboratory will perform the following tests:

1. Complete blood count (CBC) plus white blood cell differential and platelet count\*
2. Serum creatinine
3. Alanine aminotransferase (ALT)
4. HIV assay (Food and Drug Administration [FDA]-approved screening antibody assay with Western Blot Confirmation)
5. HBsAg ELISA
6. HCV assay (FDA-approved screening antibody assay and immunoblot confirmation or viral PCR confirmation)
7. Urinalysis (in the event of an abnormal urine dipstick test at the clinical trial site)\*\*

\* The following CBC parameters will be assessed for safety throughout the trial:  
WBC, ANC (absolute neutrophil count), Hemoglobin, and Platelet Count

\*\* Urine and/or serum  $\beta$ -hCG testing will be performed at the clinical trial site using FDA approved products

### **6.14 Immunologic Laboratory Testing**

#### **6.14.1 Antibody Assay (ELISA)**

Anti- Pfs25 ELISAs will be performed on sera or plasma obtained from immunized subjects at the Laboratory of Malaria Immunology and Vaccinology (LMIV) in Rockville, MD. Briefly, microwell plates are coated with antigen solution. Plates are washed with TRIS-buffered saline (TBS) containing Tween-20 (T-TBS) and blocked with TBS containing skim milk powder. After washing with T-TBS, diluted serum samples are added in triplicate and incubated at room temperature for 2 hours. After incubation, unbound antibodies are removed by washing the plates with T-TBS, and alkaline phosphatase-conjugated goat anti-human IgG solution is added to each well and incubated for 2 hours at room temperature. Plates are then washed with T-TBS, followed by adding phosphatase substrate solution to each well; the plates are then covered and incubated for 20 minutes at room temperature for color development. The plates are read immediately at 405 nm with a microplate reader. The optical density values are used to determine antibody levels by comparing to a standard curve generated from a known positive-control plasma included on each ELISA plate.

#### **6.14.2 Standard Membrane Feeding Assay (SMFA)**

Membrane feeding assays demonstrate biologic activity of transmission blocking antibody, and

are critical to selection of vaccine candidates. In a SMFA, test serum or plasma obtained from immunized subjects is mixed with parasites from a laboratory culture and the mixture is placed in a feeding cup covered with an artificial membrane. Pre-starved mosquitoes from a laboratory colony are allowed to feed through the membrane. One week after the feed, mosquitoes are dissected and midguts are stained with mercurochrome for the oocyst form of the parasite. The reduction of oocyst-laden mosquitoes or the reduction of oocyst numbers in each mosquito demonstrate biologic function of the antibody, and may be predictive of efficacy in the field. SMFA results have been shown to correlate with ELISA antibody titers against Pfs25 in several species [[Cheru et al 2010](#)].

The assay will be conducted at LMIV and the Laboratory of Malaria Vector Research (LMVR), Rockville, MD.

Additional exploratory direct membrane feeding assays will be done by the Entomology Department, Armed Forces Research Institute of Medical Sciences, Bangkok, Thailand by the Malaria Research and Training Center, Universite de Bamako, Bamako, Mali, and by the Institut de Recherche en Sciences de la Santé (IRSS), Bobo-Dioulasso, Burkina Faso (via the Institut de Recherche pour le Développement (IRD) - Montpellier, France). The assay may use gametocytes from volunteers recruited under separate local IRB-approved protocols and consents.

#### **6.14.3 B-Cell and T-Cell Assays**

Specimens collected for B cells and T cells studies will undergo initial processing and cell separation at the CIR, and will be shipped to LMIV in liquid nitrogen shippers as per SOP.

B cell studies will be done at LMIV. The analysis of the generation and maintenance of antigen-specific memory B cells will be carried out to determine if these cells can be elicited and maintained by vaccination. Peripheral blood lymphocytes will be obtained and assayed for the presence of antigen-specific memory B cells and for the total number of memory B cells using flow cytometry and ELISPOT assays.

T cell studies will be done at LMIV. Antigen-specific T cell responses to vaccination will be determined by ELISPOT and/or Intracellular Cytokine Staining flow cytometry.

### **7 Use, Storage, and Tracking of Specimens and Data**

Samples and data collected under this protocol will be used to study malaria and related diseases, and possible adverse reactions to vaccination. Access to research samples will be limited using either a locked room or a locked freezer. Samples and data will be stored using codes assigned by the investigators or their designees. Data will be kept in password-protected computers. Only investigators or their designees will have access to the samples and data.

Samples will be stored at the LMIV in Rockville, MD or at LMIV's designated repository, Thermo Scientific, Rockville, MD with the exception of retention specimens which may be kept at the CIR for quality control. Samples may also be stored at LMVR, NIAID, a laboratory

designated by the PATH Malaria Vaccine Initiative. Samples will be tracked using a sample tracking software program, e.g., Freezerworks. Any loss or unanticipated destruction of samples (for example, due to freezer malfunction) or data (for example, misplacing a printout of data with identifiers) will be reported to the IRBs. Such a loss will be reported to the NIAID IRB as a protocol violation under the following classification: the violation compromises the scientific integrity of the data collected for the study.

## **8 Retention of Specimens for Future Use**

Specimens collected as part of this trial will be stored for future research. These samples may be used to learn more about malaria infection and other diseases. These samples will not be sold or used to make commercial products. The subject may withdraw permission for future use of specimens at any time. If a subject withdraws his or her permission for future use of specimens, those specimens will be destroyed. All samples stored will be labeled with the subject's study identification (ID) number, which cannot identify the study subject but is linkable to other research databases (e.g., questionnaires, clinical assessments, logbooks) generated by the main study. The database will contain only the study subject's ID number. A master log linking the study subject ID number to the name of the subject will be maintained in a password protected database system with access limited to authorized research team members. In the event of samples being requested in the future, only the site Investigators or site study coordinator will have access to the log linking the study subject to the samples.

At the completion of the protocol (termination), samples and data will either be destroyed, or transferred to another existing protocol, "Research Use of Human Specimens", NIAID Protocol #08-I-N064. In the future, other investigators may wish to study these samples and/or data. If so, the National Institutes of Health (NIH) and/or the PATH Malaria Vaccine Initiative may send samples to the other investigators. In that case, IRB approval must be sought prior to any sharing of samples. Any clinical information shared about the sample with or without patient identifiers would similarly require prior IRB approval. The research use of stored, unlinked, or unidentified samples (for example, as a standard for immunological analyses) may be exempt from the need for prospective IRB review and approval. Exemption requests will be submitted in writing to the NIH Office of Human Subjects Research (OHSR), which is authorized to determine whether a research activity is exempt.

## **9 Safety and Adverse Event Reporting**

### **9.1 Definitions**

#### **Adverse Events**

An adverse event (AE) includes any untoward or unfavorable medical occurrence in a human subject, including any abnormal sign (e.g. abnormal physical exam or laboratory finding), symptom, or disease, temporally associated with the subject's participation in the research, whether or not considered related to the research. This includes an exacerbation of pre-existing conditions and intercurrent illnesses. All AEs will be graded for severity and assessed for

relationship to the investigational vaccine as described below.

